## Methods

### Trial Design

This study will be a randomized, two-arm trial in which intermediate and high-risk prostate cancer patients are treated with both HDR brachytherapy and EBRT. In Arm A, patients will receive HDR brachytherapy before EBRT. In Arm B (control arm), patients will receive EBRT before HDR brachytherapy. The assessment of the acute and late toxicities at various time points will be carried out. The treatment should start within 3 months from the randomization date. This trial has been registered with the International Standard Randomized Controlled Trial Number (ISRCTN) registry (ISRCTN: 15835424).

Toxicity will be assessed using the following tools:

1. International Prostate Symptom Score (IPSS)

2. International Index of Erectile Function Scale (IIEFS)

3. Functional Assessment of Cancer Therapy-Prostate (FACT-P), version 4

4. National Cancer Institute Common Terminology Criteria for Adverse Events (CTCAE), version 4, grading system

The THEPCA study scheme design is shown in Figure 1.

**Figure 1 figure1:**
[figure not shown]
THEPCA study scheme design.

### Number of Participants and Participant Selection

A total of 50 patients will be recruited to the whole study, which includes both arms of the study for evaluation of the outcomes. It is estimated that the dropout rate due to screen failures will be approximately 10%. Inclusion and exclusion criteria for the study are shown in Textbox 1.

Inclusion and exclusion criteria for the THEPCA study.Inclusion Criteria18 years of age or olderHistologically diagnosed prostate cancer (stages T1b-T3bN0M0)Any Gleason scoreAny PSA levelPatient must be able to provide consent and fill in the questionnairesExclusion CriteriaPrevious transurethral resection of the prostate (TURP)/holmium laser enucleation of the prostate (HoLEP) laser prostatectomyAny metastatic diseaseAn IPSS greater than 20Pubic arch interferenceLithotomy positionAnesthesia is not possibleRectal fistulaPrior pelvic radiotherapy

### Study Procedures

#### Screening Procedures

Patients will undergo the following procedures as per the standard of care, the results of which will be communicated to the investigator for their review prior to approaching the potential participant: tumor staging (CT/MRI/bone scans), histological confirmation of diagnosis (Gleason score), and PSA measurement.

#### Informed Consent and Randomization Procedures

##### Overview

It is the responsibility of the investigator, or an appropriately trained person (ie, trained in Good Clinical Practice [GCP]) delegated by the investigator as documented in the site delegation log, to obtain written informed consent from each participant prior to any participation-/study-specific procedures. This will follow adequate explanation of the aims, methods, anticipated benefits, and potential hazards of the study.

The participant will be given ample time to consider giving their informed consent for the study—for this study, 24 hours will be given during which time the consenting physician will be reachable by phone to answer any questions. The date that the Participant Information Sheet (PIS) is given to the participant will be documented within the patient’s notes to ensure that sufficient time was given.

If, for some reason, the consenting physician is not accessible by phone and the participant wishes to speak with them, a second consent visit should be arranged.

The investigator, or other qualified person, will explain to the potential participant that they are free to refuse involvement with any part of the study, or alternatively may withdraw their consent at any point during the study for any reason.

If there is any further safety information which may result in significant changes in the risk/benefit analysis, the PIS and the Informed Consent Form (ICF) will be reviewed and updated accordingly. All participants that are actively enrolled in the study will be informed of the updated information and given revised copies of the PIS and ICF in order to confirm their wish to continue in the study.

##### Randomization

Randomization will be carried out by the clinical trials data manager within the Anglia Ruskin Clinical Trials Unit (ARCTU) at Anglia Ruskin University (ARU). ARCTU uses the Trans European Network ALEA (TENALEA) randomization service provided by the Trans European Network for Clinical Trial Services. This is an Internet-based randomization system, which will be set up for the study by ARCTU in accordance with the protocol. It will be a simple 1:1 ratio randomization, which will only be possible if a participant meets the inclusion criteria and not the exclusion criteria. The system stores the predetermined sequence of randomization—this list is not visible to the investigator or to the Anglia Ruskin Clinical Trials Unit. Once a patient has consented to take part in the trial, they will be randomly allocated to either Arm A or Arm B. The research nurse or investigator will log onto the Web browser application and enter the patient’s eligibility and stratification factors into the system. The study arm allocation is then returned to the investigator and to selected members of ARCTU and the study team. Please refer to the study scheme diagram in Figure 1.

#### Baseline Procedures

The following baseline procedures will be performed: physical examination, measurement of vital signs, and assessment of QoL baseline (IPSS, IIEFS, FACT-P, CTCAE questionnaires), hematology, biochemistry, concomitant treatment (eg, androgen deprivation therapy [ADT]), and PSA.

#### Treatment Modalities

#####  Brachytherapy Procedure

The brachytherapy procedure will be carried out at the surgical theaters in Southend University Hospital. The steps are as follows:

1. Patients will undergo prostate implantation under general or spinal anesthetic using a transrectal ultrasound-guided transperineal technique.

2. Imaging according to local practice using ultrasound, CT, and/or MRI will be undertaken.

3. The clinical target volume for prostate (CTVp) is defined by the prostate capsule and is extended to include any extra capsular or seminal vesicle disease. A volumetric expansion of 3 mm constrained to the rectum posteriorly is then added—this defines the planning target volume (PTV).

4. Catheter reconstruction and dwell time definition is then undertaken to provide a treatment plan for approval by the treating clinician.

5. Treatment is delivered once an optimized plan has been approved.

6. After completion of treatment in the brachytherapy room, the implant catheters and urinary catheter are removed—no anesthesia is required for this procedure.

7. The patient will return to the ward and may be discharged home later the same day or the following day.

##### Dose Prescription

A dose of 15 Gy will be given in a single treatment exposure defined at 100% isodose, which is the minimum tumor isodose to cover the PTV. PTV recommendations are as follows: the minimum dose received by 90% of PTV (D90) should be ≥15 Gy, and the volume of the target area receiving 100% of the prescribed dose (V100) should be ≥95%. See Table 1 for the risk-tolerance doses of the rectum and urethra.

**Table 1 table1:** Organs at risk-tolerance doses.

Organ	Risk-tolerance dose
Rectum D2cc^a^	12 Gy
Rectum V100^b^	0 cc
Urethra D10^c^	<17.5 Gy
Urethra D30^d^	<16.5 Gy
Urethra V150^e^	0 cc

^a^Dose to 2 cm^3^(D2cc).

^b^Volume of target area receiving 100% of prescribed dose (V100).

^c^Dose covering 10% (D10) of the urethral volume.

^d^Dose covering 30% (D30) of the urethral volume.

^e^Volume of target area receiving 150% of prescribed dose (V150).

##### External Beam Radiotherapy

EBRT will be given to prostate and seminal vesicles only, using either intensity-modulated radiotherapy or volumetric-modulated arc radiotherapy (VMAT) to a dose of 46 Gy in 23 fractions over 4½ weeks. The dose-volume histogram (DVH) would be according to the local radiotherapy protocol. The gap between BT and EBRT, irrespective of their sequence, should not exceed 3 weeks. Therefore, the total radiotherapy treatment time should be up to 7½ weeks.

### Androgen Deprivation Therapy

Patients will receive neoadjuvant and adjuvant antiandrogen therapy from 6 months to 3 years according to the risk stratification of the disease as per the standard of care.

Table 2 shows the schedule of assessments throughout the study.

**Table 2 table2:** Schedule of assessments during the study.

Steps and assessments	Pretreatment time points	Treatment time points		Posttreatment time points^a^				
	Screening^b^and consent	Baseline	Start of second treatment^c^	6 weeks	3 months	6 months	9 months	12 months
Informed consent	*							
Physical examination		*	*	*	*	*	*	*
Vital signs		*	*	*	*	*	*	*
QoL, IPSS, IIEFS, FACT-P, CTCAE^d^		*			*		*	*
Hematology		*						*
Biochemistry		*						*
Concomitant treatment (eg, ADT^d^)		*	*	*	*	*	*	*
Tumor staging	*							
Histological confirmation of diagnosis	*							
PSA^d^	*	*			*	*	*	*
RT^d^and brachytherapy dose				*				

^a^assessments performed after complete treatment

^b^screening procedures carried out as per standard of care

^c^start day of second treatment modality

^d^Quality of life (QoL), International Prostate Symptom Score (IPSS), International Index of Erectile Function Scale (IIEFS), Functional Assessment of Cancer Therapy-Prostate (FACT-P), Common Terminology Criteria for Adverse Events (CTCAE), androgen deprivation therapy (ADT), prostate-specific antigen (PSA), radiotherapy (RT).

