#### Secondary Endpoint Efficacy Analysis

For the IPSS and IIEFS scale scores, the two means at each of the follow-up assessments will be compared using a two-sided permutation *t* test, and the 95% confidence limits for the difference between the means will be calculated using a bootstrap method. There will also be an assessment of trends in the scores over time using a repeated measures analysis of variance on the four follow-up scores, with the baseline score as a covariate. Prostate-specific antigen relapse-free survival will be estimated using the Kaplan-Meier method, with a test for the difference between the survival curves using the log-rank test. Cox proportional hazards multiple regression will also be used to assess the effects of covariates on survival. For this feasibility study, this analysis will be carried out after the end of the follow-up at 12 months, whereas for a main study a longer follow-up period would be considered.

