#### Statistical Analysis

Although the sample size will be small, there will nevertheless be attempts to analyze the data in the same way as would be the case for a main study. However, this might not always be possible depending on the pattern of the outcomes and missing values. For descriptive statistical summaries, continuous data will be summarized using means, medians, standard deviations, interquartile ranges, and ranges. Categorical data will be summarized using counts and percentages. All statistical significance testing will be at the 5% significance level. For the IPSS and IIEFS scale scores, the two means at each of the follow-up assessments will be compared using a two-sided permutation *t* test using 1,000,000 random permutations, and the 95% confidence limits for the difference between the means will be calculated using a bootstrap method using 9999 resamplings. There will also be an assessment of trends in the scores over time using a repeated measures analysis of variance on the four follow-up scores with the baseline score as a covariate.

For categorical data based on adverse events, percentages will be compared using Fisher’s exact test. In this small study it will be possible to carry out the full combinatorial calculations for Fisher’s exact test, whereas in a main study, 10,000 random permutations will be obtained in a Monte Carlo approach. For differences between percentages, the 95% confidence limits will be obtained using Newcombe’s Hybrid Score Interval method. For the secondary analysis, prostate-specific antigen relapse-free survival will be estimated using the Kaplan-Meier method, with a test for the difference between the survival curves using the log-rank test—the *P* value will be obtained using a permutation test with 10,000 permutations. Cox proportional hazards multiple regression will also be used to assess the effects of covariates on survival, with model comparisons carried out using likelihood ratio tests. The analyses will be performed using the computer program R. All randomized participants will be included in the analyses. There are no planned interim analyses.

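### Neither planned IIEFS analysis uses planned ADT or risk group, although ADT length differs widely between men; a pre-randomization ADT covariate is a cheap gain in a secondary analysis

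*Protocol article*

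**What the plan says.** On hormone treatment, the Androgen Deprivation Therapy section of the protocol article states: "Patients will receive neoadjuvant and adjuvant antiandrogen therapy from 6 months to 3 years according to the risk stratification of the disease". Trial Design describes the population as intermediate and high risk, so a mixture of courses is to be expected. The same section lists IIEFS among the toxicity tools and says: "The treatment should start within 3 months from the randomization date".

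On the scores, the Statistical Analysis section states: "For the IPSS and IIEFS scale scores, the two means at each of the follow-up assessments will be compared", with a permutation *t* test and a bootstrap interval. Secondary Endpoint Efficacy Analysis adds a "repeated measures analysis of variance on the four follow-up scores, with the baseline score as a covariate". Covariates other than baseline score appear only for PSA relapse-free survival: "Cox proportional hazards multiple regression will also be used to assess the effects of covariates on survival".

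On data and allocation, ADT is the named example of concomitant treatment in Baseline Procedures, and Table 2 marks concomitant treatment at every later visit. Table 2, as it can be read, marks the questionnaires at baseline and at 3, 9 and 12 months after completed treatment. The Randomization section describes simple 1:1 allocation, but also has staff enter stratification factors that are not named anywhere.

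**The concern.** IIEFS measures erectile function, on which ADT can be expected to act; the documents give no figure for that effect. A 6-month course that begins before radiotherapy will have ended by 9 and 12 months after treatment. A 3-year course will normally still be running. The arm means at those visits then probably combine men in different hormonal states, in proportions left to chance.

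Adjusting for baseline score does not fully deal with this. Part of the course is neoadjuvant and radiotherapy may start up to 3 months after randomization, so some baseline scores may be taken on ADT and others before it. The documents do not give the timing, so this is an inference. In either case, ADT that starts or stops after baseline is not captured by the baseline score.

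At stake are the precision of the IIEFS comparison and how an IIEFS difference is read in a single small trial whose arms happen to differ in planned ADT. Neither the validity of the randomization nor the primary endpoint is at issue.

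**Working it through.** There is no stated power or effect size to reproduce; the Sample Size section says that the 50 patients were not chosen on statistical grounds.

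**Inputs from the protocol.** 25 per arm; simple 1:1 allocation; 5% significance level; baseline score as the only covariate for the scores.

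**Assumptions (not in the protocol).** Share *q* of men planned for long-course ADT: 0.3 to 0.5 (0.7 was also simulated). Effect *g* of being on long-course ADT on a late IIEFS score: 0.3, 0.5, 1.0 or 1.5 within-group SD. Correlation of baseline with follow-up score: 0.5.

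**1. Chance imbalance.** Take two independent Binomial(25, *q*) counts. A 20-point difference is 5 of 25 men.
- *q* = 0.3: P(difference of 5 or more) = 0.164
- *q* = 0.5: P = 0.203

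The average imbalance in those trials is 0.24 to 0.25.

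**2. Shift in an imbalanced trial.** The expected shift is about imbalance × *g*, for example 0.25 × 1.0 = 0.25 SD. A simulation (40,000 trials per setting, *q* = 0.3, 0.5 and 0.7, no sequence effect, ordinary *t* test standing in for the permutation test) gave, in trials with an imbalance of 20 points or more:

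| ADT effect *g* (SD) | Mean shift (SD) | False positives, unadjusted |
|---|---|---|
| 0.3 | 0.07–0.08 | about 6% |
| 0.5 | 0.12–0.13 | about 7% |
| 1.0 | 0.24–0.25 | about 10% |
| 1.5 | 0.36–0.38 | about 14% |

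Adjusted for the ADT indicator, false positives in the same trials were 4.6 to 5.3%. Over all trials, imbalanced or not, the unadjusted test rejected in 4.8 to 5.2% and the mean difference was about 0.

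**3. Precision against the visit-wise unadjusted test.** For a true sequence effect of 0.8 SD, unadjusted power was 77 to 79% for *g* of 0.3 to 0.5, 70 to 72% at 1.0 and 60 to 63% at 1.5. With the ADT covariate it was 78 to 79% throughout.

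**4. Precision against the planned baseline-adjusted model.** This is the fairer comparator. With correlation 0.5 the residual variance is 1 − 0.5² = 0.75. Leaving ADT out adds *g*²*q*(1 − *q*). Fitting one more term takes the residual degrees of freedom from 47 to 46. The ratio of standard errors is therefore about √[0.75 / (0.75 + *g*²*q*(1 − *q*))] × √(47/46). At *q* = 0.5:
- *g* = 0.3: √(0.75/0.7725) × 1.011 = 0.996, a cut of 0.4%
- *g* = 0.5: √(0.75/0.8125) × 1.011 = 0.971, a cut of 2.9%
- *g* = 1.0: √(0.75/1.00) × 1.011 = 0.875, a cut of 12.5%
- *g* = 1.5: √(0.75/1.3125) × 1.011 = 0.764, a cut of 23.6%

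A direct simulation of both models at *q* = 0.5 gave ratios of 0.991, 0.969, 0.878 and 0.762.

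**The case against.** The strongest reply is that randomization already deals with this. ADT is set by risk group as standard of care, not by arm. Chance imbalance in a prognostic factor is part of what the test and interval allow for, and the simulation agrees. That stands. A reader might infer that the arms are unbalanced by design, or that an ADT imbalance would be taken for a sequence effect. The documents support neither. Even after a large imbalance the shift is 0.25 SD for a 1.0 SD effect, against the 0.79 SD that 25 per arm can detect with 80% power: (1.96 + 0.84) × √(2/25).

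It is also tempting to say that the scores mostly follow each man's ADT course. The documents give no ADT effect on either score, and even an assumed 1.5 SD effect explains only 32 to 36% of the variance. For IPSS nothing in the documents points to an ADT effect. Nor are the scores compared only as raw means, since the repeated measures model adjusts for baseline.

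A further reply is that covariates for a secondary score belong in an analysis plan that is not shown. That carries some weight. But the article fixes these analyses closely, down to the numbers of permutations and resamples and the single covariate, so improving a method it states is a fair comment. The unnamed stratification factors might include risk group; balance on risk can be neither assumed nor ruled out.

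**Conclusion.** The point holds as a modest improvement to a secondary analysis. The IIEFS comparison is valid on average, but omits a plausible prognostic factor that can be known before randomization. Under the assumed shares, 16 to 20% of trials of this size would have an imbalance of 20 points or more in long-course ADT. The consequence is a possible shift in the IIEFS difference in such a trial, and some loss of precision. The loss is negligible if the ADT effect is 0.3 to 0.5 SD and material at 1.0 SD or above. The size of the ADT effect, the long-course share and the baseline correlation are all assumptions. The grade 3 genitourinary endpoint, tested by Fisher's exact test, is untouched.

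**What to change.** In Secondary Endpoint Efficacy Analysis and Statistical Analysis, add two covariates to the IIEFS model alongside baseline score: planned ADT duration (or risk group), and whether ADT has already started. Both should be fixed before randomization. Make the adjusted estimate the main IIEFS comparison and keep the unadjusted visit-wise tests as supporting results. Do not adjust for ADT actually received after randomization, because that could itself be affected by allocation. For IPSS the same adjustment is optional. In the Randomization section, reconcile simple allocation with the stratification factors and name any that are used.

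The cost is at most two CRF fields and up to two degrees of freedom in 50 patients. Risk group can be derived from the stage, Gleason score and PSA already collected at screening, and concomitant ADT is already recorded at baseline. No change to treatment is involved.

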**Objective:**

Assessment of acute genitourinary and gastrointestinal toxicities at various time points to better understand if the order in which treatment modality is delivered (ie, HDR brachytherapy or EBRT first) has an effect on the toxicity profile.

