### Rationale and Risks/Benefits

There is no consensus about the timing of HDR brachytherapy when treating prostate cancer along with EBRT. The advantages of using HDR brachytherapy before EBRT are that patients could potentially be identified who are not suitable for brachytherapy early in the treatment process. As the patients would be radiotherapy naïve, there would be less chance of soft tissue injury during the brachytherapy process if BT is given first. However, having brachytherapy first can be logistically difficult in a busy radiotherapy unit in terms of planning and arranging delivery of EBRT within 2 to 3 weeks of BT. Moreover, if the patients develop acute urinary complications during brachytherapy they would need to continue with EBRT with a urinary catheter, which could potentially prolong the duration of the catheter in situ and cause significant patient discomfort.

On the other hand, delivering EBRT first is logistically easier to arrange and could theoretically make the hypofractionated radiation dose of brachytherapy more effective, as tumor cells could become more radiosensitive due to molecular changes having been induced by EBRT. However, normal tissue damage due to delivery of EBRT first could make the brachytherapy procedure difficult with increased risk of toxicity. It is, therefore, essential to know whether there are any significant differences in toxicities and treatment outcomes, especially acute urinary toxicity among the two treatment approaches.

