#### Primary and Secondary Endpoints

The primary endpoint of this study is the presence of grade 3 genitourinary toxicity in patients. The secondary endpoints of this study are the presence of all other grades of genitourinary toxicity (ie, grades 1 and 2), the presence of gastrointestinal toxicity (ie, grades 1 to 4), prostate-specific antigen (PSA) recurrence-free survival, overall survival, and quality of life (QoL).

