##### Severity

The investigator must assess the severity of the event according to the following terms and assessments. The intensity of an event should not be confused with the term “serious” which is a regulatory definition based on participant/event outcome criteria.

1. Mild: intensity of an event is mild if some discomfort is noted, but without disruption of daily life.

2. Moderate: intensity of an event is moderate if discomfort is enough to affect/reduce normal activity.

3. Severe: intensity of an event is severe if it causes a complete inability to perform daily activities and lead a normal life.

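### Table 2 schedules no CTCAE or IPSS assessment between baseline and 3 months after both modalities, and the AE severity scale used in between is not mapped to CTCAE grades

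*Protocol article*

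**What the plan says.** The abstract gives the objective as "Assessment of acute genitourinary and gastrointestinal toxicities at various time points". Rationale and Risks/Benefits asks about differences in toxicity and outcome, "especially acute urinary toxicity among the two treatment approaches", and both that section and Trial Design speak of acute and late toxicity. Under Primary and Secondary Endpoints, "The primary endpoint of this study is the presence of grade 3 genitourinary toxicity in patients"; grades 1 and 2 genitourinary and grades 1 to 4 gastrointestinal toxicity are secondary. Of the four tools listed in Trial Design, the only one described as a grading system is "National Cancer Institute Common Terminology Criteria for Adverse Events (CTCAE), version 4, grading system".

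Table 2 sets the timing. The row "QoL, IPSS, IIEFS, FACT-P, CTCAE" is marked at baseline, 3, 9 and 12 months. It is blank at the start of the second treatment, at 6 weeks and at 6 months. Physical examination and vital signs are marked at all of these visits. A footnote says that the posttreatment columns are "assessments performed after complete treatment".

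Between visits, the section on notification of adverse events requires non-serious events to be documented in the CRF. The Severity section rates events on three levels, the top one being "Severe: intensity of an event is severe if it causes a complete inability to perform daily activities and lead a normal life".

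**The concern.** Acute toxicity is toxicity during and soon after radiotherapy, and the schedule has no CTCAE grade or IPSS score in that window. The protocol itself expects events there. Rationale and Risks/Benefits describes acute urinary complications of brachytherapy that carry over into EBRT with a catheter. Participant Withdrawal lists catheterization for blockage during EBRT.

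If such an event resolves before 3 months, the scheduled grading either misses it or depends on recall. The adverse event record may hold it, but with a severity term that the protocol does not convert to a CTCAE grade. Both the primary endpoint and the lower-grade secondary endpoints are affected, and no later analysis can recover grades that were not collected.

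The posttreatment clock starts when both modalities are complete. The delay between a given modality and its first grading therefore depends on the order of treatment, which is what the trial randomizes.

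**Working it through.** **Inputs**
- EBRT: "46 Gy in 23 fractions over 4½ weeks" (External Beam Radiotherapy). HDR is a single exposure (Dose Prescription), taken here as having no duration.
- Gap between modalities: at most 3 weeks (External Beam Radiotherapy). The range 0 to 3 weeks is used.
- First marked CTCAE/IPSS after baseline: 3 months after both modalities (Table 2), taken as 13 weeks.

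**Plan's own figure for treatment time.** 4.5 + 3 = 7.5 weeks, which agrees with the stated maximum.

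**Reading of the table.** The row has eight cells, with marks at baseline, 3, 9 and 12 months. The physical examination and PSA rows fit the same eight columns, so a column shift in the extracted text is unlikely.

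**First radiation to first scheduled grade**
- No gap: 4.5 + 0 + 13 = 17.5 weeks.
- 3-week gap: 4.5 + 3 + 13 = 20.5 weeks.

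**Lag to first scheduled grade, by arm**

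| Measured from | Arm A (HDR first) | Arm B (EBRT first) |
|---|---|---|
| HDR | 17.5 to 20.5 weeks | 13 weeks |
| End of EBRT | 13 weeks | 13 to 16 weeks |

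The HDR lag is longer in Arm A by 17.5 − 13 = 4.5 to 20.5 − 13 = 7.5 weeks.

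**Number of follow-up scores.** Secondary Endpoint Efficacy Analysis and Statistical Analysis both plan a repeated measures analysis of four follow-up values of IPSS and IIEFS, with baseline as covariate. Table 2 gives three (3, 9 and 12 months). The plan's four is not reproduced unless baseline is counted, and baseline is the covariate. One mark may therefore be missing:
- If it is 6 months, the acute gap is unchanged.
- If it is 6 weeks, the gap after treatment falls from 13 to 6 weeks. First radiation to first grade becomes 4.5 + 0 + 6 = 10.5 to 4.5 + 3 + 6 = 13.5 weeks. The HDR lag is then 10.5 to 13.5 weeks in Arm A and 6 weeks in Arm B, still 4.5 to 7.5 weeks apart.
- In both cases nothing is graded during treatment.

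**Size against expected events.** At the grade 3 rate quoted in Rationale and Risks/Benefits (1.6%), 50 × 0.016 = 0.8 events are expected, and the chance of none is 0.984^50 = 0.45. For grade 2, the Background quotes 62% from a single-arm study that used a different EBRT schedule. If that rate applied here, 0.62 × 50 = 31 patients would have an acute grade 2 genitourinary event, so a secondary endpoint has far more to lose in number.

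**The case against.** The strongest reply is that toxicity does not depend on the schedule alone. Adverse events go into the CRF whenever they occur, Safety Endpoints says that the primary endpoint concerns adverse events, and Statistical Analysis applies Fisher's exact test to categorical adverse event data. Hospitalization makes an event serious, and catheterization during EBRT is a listed reason for withdrawal from treatment. This stands: acute events would probably be recorded. What is missing is a rule turning the three severity terms into CTCAE grades, so the record does not by itself yield the endpoint. An article may leave CRF detail to the full protocol, but this one prints both a complete schedule and a severity scale, and the two do not fit the endpoint.

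It also stands that Table 2 may lack a mark, possibly at 6 weeks. That lowers confidence in the 13-week posttreatment figure, but not in the absence of on-treatment grading. The primary objective and endpoint do not themselves say acute, so acute toxicity is a central aim rather than the only one.

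Four stronger readings are tempting and are not supported:
- *A reader might infer that an event must last 13 weeks to be counted.* That holds only if CTCAE is graded on current status. The protocol does not say whether a visit grade is current or worst since the last visit.
- *A reader might infer that the schedule makes the arms look alike.* The lags differ by arm, so the gap could hide a difference or distort one. The direction is not known.
- *A reader might infer that one lost grade 3 event overturns the primary test.* With 25 per arm, Fisher's exact test gives p = 0.110 for 4 against 0, 0.0502 for 5 against 0 and 0.022 for 6 against 0. With 0.8 events expected, one more or fewer would not change the conclusion. Rarity is a separate matter, and the protocol says that the sample size was not statistically derived.
- *A reader might infer that a grade at the start of the second treatment answers the sequence question.* At that visit Arm A has had only HDR and Arm B only EBRT, so the comparison is between modalities.

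**Conclusion.** The concern holds as a defect of ascertainment. On the printed table no CTCAE or IPSS assessment is scheduled for 17.5 to 20.5 weeks after the first radiation, and two existing visits inside that window carry neither. The adverse event record covers the interval on a scale not mapped to the CTCAE grades that define the toxicity endpoints. The lag from HDR to first grading differs between arms by 4.5 to 7.5 weeks, so the timing of ascertainment follows the randomized sequence.

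The figures assume 3 months is 13 weeks, a gap of 0 to 3 weeks and an HDR procedure of negligible length. The conclusion that nothing is graded during treatment does not depend on which mark, if any, is missing from Table 2. The 13-week posttreatment gap does, and would be 6 weeks if the missing mark is at 6 weeks. How many events would be lost, and in which arm, cannot be estimated from the document.

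**What to change.** 1. In Table 2, mark CTCAE and IPSS at the existing start-of-second-treatment and 6-week visits.
2. At every visit, including 6 months, record the worst CTCAE version 4 grade since the previous visit. This matters beyond adding marks. Even after the change, the first grade after HDR comes at 0 to 3 weeks in Arm A and at 6 weeks in Arm B; worst-grade recording makes the periods covered continuous in both arms.
3. Grade all adverse events by CTCAE version 4, in place of or alongside the terms in the Severity section, and state that between-visit events count toward the primary endpoint.
4. Reconcile the four follow-up scores in Secondary Endpoint Efficacy Analysis and Statistical Analysis with the amended table. Use posttreatment IPSS only: 6 weeks plus 3, 9 and 12 months gives four. Report the start-of-second-treatment score descriptively, since the arms then differ in modality received; including it would give five. IIEFS shares the same analysis sentence, so either collect it at 6 weeks too or state that it has three scores.

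The cost is some extra grading and one questionnaire at two visits patients already attend, added CRF fields and a protocol amendment. No new visit is needed.
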